### Assignment of interventions: allocation and blinding

Restricted randomisation will be used to allocate the 60 clusters into the three study arms. Arms will be balanced on the following criteria: population size of the cluster (required to balance net numbers), infection prevalence, and socio-economic status. Data on these variables by cluster will be obtained through the pre-trial (baseline) cross-sectional survey.

The study is a single-blinded trial. Study participants will be blinded to the type of nets they have received. All field staff will be blinded to the allocation and analyses will be conducted on blinded data.

### Data collection, management, and analysis

#### Census

A short questionnaire will be used to collect demographic details on household residents to estimate the number of nets required to be distributed in each house and to randomly select children for the cohort. Each building will be mapped using a Global Positioning System to assist with delineating clusters.

#### Cohort monitoring

All children included in the cohort will be cleared of infection at enrolment using directly observed treatment with artemisinin-based combination therapy (ACT). During follow-up, visits will take place every two weeks during the malaria transmission season (from April to November) and every month during the dry season (from December to March). During each visit, children with fever (temperature ≥ 37.5 °C) or reporting a fever in the past 48 h will be tested for the presence of malaria parasites using RDT (SD Bioline Malaria Ag P.f, HRP2, Standard Diagnostics, Germany). If a child has a positive RDT, they will be recorded as a malaria case and will receive treatment as per national guidelines [40].

During the enrolment visit, a detailed questionnaire will be administered, to collect information on net ownership, household assets (as a proxy for socioeconomic status) and housing materials and window screening, and a clinical examination of the child will be conducted. In follow-up visits, a short questionnaire will be administered to record information on LLIN usage the night before, any adverse events encountered, and travel history. At each visit, children will also be examined by study nurses for signs of other illnesses and will be treated if needed. A child will be considered “lost to follow-up” if they miss at least 4 consecutive visits (i.e. 8 weeks of follow-up time).

#### Cross-sectional surveys

Each survey will include two components; i) a household survey and ii) a clinical survey. During the household survey, a questionnaire will be administered to obtain information on demographic and socioeconomic data, educational status, wealth assets of the household, vector control measures, and randomly sampled persons (2 per household) will be tested for malaria using an RDT, regardless of symptoms. Haemoglobin level will be measured with an HemoCue device (HemoCue Hb 201+, Aktiebolaget Leo Diagnostics, USA) in children under 5 who will receive iron tablets if they are found to be anaemic. Information will be collected on the perception and acceptance of nets. The occurrence of adverse events will also be reported.

#### Entomology activities

Entomological monitoring will take place every 3 months in each of the 60 study clusters. A standardized questionnaire will be used in each selected household to record the number of inhabitants, type of house (wall, roof, number of rooms, number of sleeping places), presence of animals, and malaria prevention measures used by household members. Mosquito collections will take place using HLCs. Four trained volunteer mosquito collectors from each study cluster will participate in house collections; one will be seated indoors and the second outdoors, and both will be replaced after 6 h of collection by the other two collectors. The collectors will be supervised by a team leader during the collection night.

Mosquitoes collected will be identified by microscopy and the numbers of *An. gambiae* s. l., *An. funestus* s. l. and other anophelines recorded [41]. Human biting rate (outdoor and indoor) will be compared between study arms. Parity rates will be estimated in a subset of live *Anopheles* mosquitoes through dissection of ovaries [42]. The presence of *Plasmodium falciparum* circumsporozoite protein (Pf-CSP) in *Anopheles* vectors will be identified in a sub-sample (minimum of 50 *Anopheles* from indoor and outdoor collections per house) using an enzyme-linked immunosorbent assay (ELISA) [43]. All *An. gambiae* s.l. positive for Pf-CSP and a sub-sample of negative specimens will be identified to species-level by PCR [44]. The EIR will be calculated as the aggregated mean of sporozoite infective bites/person/year. In order to assess the impact of the pyrethroid-pyriproxyfen LLIN (Royal Guard®) on mosquito reproduction, blood-fed *Anopheles* will be collected and ovary development recorded each year in houses from study arms, by dissection.

Insecticide resistance will be monitored annually using standard CDC intensity bottle assays [45] in the three arms to determine the prevalence of any selection of resistance to pyriproxyfen or chlorfenapyr, or change in resistance to pyrethroids. To monitor changes in insecticide resistance, adult *Anopheles* will be tested in CDC bottle bioassays using discriminating dosages of alpha-cypermethrin (12.5 μg/ml), chlorfenapyr (100 μg/ml) and pyriproxyfen (100 μg/ml) [46]; where mosquito mortality is < 90% to alpha-cypermethrin, intensity assays, testing two, five and ten times the discriminating dose will be performed. The percentage mortality at 30 min and 24, 48, and 72 h post-exposure will be recorded. Mosquitoes exposed to pyriproxyfen will be dissected to assess ovary development [47]. Tests will be performed at baseline and once per year post-intervention in two clusters per study arm.

All knockdown/dead mosquitoes after insecticidal exposure and surviving 72 h post-exposure to insecticides will be stored individually in RNAlater® and preserved at − 20 °C for gene expression analysis. Following species identification by PCR, RNA will be extracted from pools of confirmed *An. gambiae* s.s. or *An. coluzzii* and cDNA synthesized, according to standard procedures. Relative expression of CYPs and other metabolic enzymes, previously identified as being over-expressed in resistant *An. gambiae* s.l. will be measured using multiplex TaqMan RT-qPCR assays [48].

### Data management

Household data, clinical measurements in the cohort study, and entomological data collected during the cross-sectional surveys will be captured in electronic forms on smartphones installed with Open Data Kit (ODK) collect. The data will be stored on a secure server located at the London School of Hygiene and Tropical Medicine (LSHTM) and all data management and analyses will be done using Stata software.

#### Data quality and control (QC)

Standard operating procedures (SOPs) for data collection will be developed and field study staff will be appropriately trained to ensure rigorous data collection. QC will be conducted by a supervisor who will monitor the performance of field staff by checking for completeness and internal consistency of responses on the same day as data collection. Data collected on paper forms (mosquito identification, insecticide resistance results) will be double entered into a database independently by two data clerks. During the study, the data manager will prepare regular QC reports to document the status of data entry and any corrective actions needed.

##### Data security

All data will be uploaded into a secure server on the LSHTM cloud. Data will be stored encrypted and will be accessible only by secure encryption keys and passwords. Access to the data will be restricted only to authorised study investigators and data management staff. A unique identifier number will be given to each participant and household to safeguard confidentiality.

##### Data storage

Upon completion of the study, electronic files will be stored on a server and also copied to encrypted USB and stored offsite in a safe box. Case report forms (CRFs) will be stored in the secure archive equipped with locked cabinets for long-term storage. Electronic data and paper source records will be retained for a minimum of 10 years following the study completion.

### Statistical methods

Descriptive statistics will be used to compare the characteristics of participants between the study arms. All primary analyses will be conducted by intention to treat and adjusted for the restriction variables used for the constrained randomisation.

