**Fig. 2 Fig2:**
[figure not shown]
Summary of study design

Each cluster will be comprised of 1 village or a group of villages for an average of 200 households (1200 residents) per cluster. Clusters will have a minimum of 100 children and 100 households. A “fried egg” design will be used for cluster boundaries. Clusters will be designed with core and buffer areas to reduce the likelihood of spill-over of intervention effects. Nets will be distributed to all households in a cluster (i.e. core and buffer areas) but data collection to measure intervention effects will be restricted to households situated in the core areas to avoid spillover from neighbouring clusters receiving different nets. The cluster demarcation will be performed using the spatial analyst toolbox in ArcGIS (ESRI, Redlands, USA) based on the following criteria; a minimum of 50 children aged 6 months to 10 years in the core area and a buffer of minimum 1000 m between core households and any households in an adjacent cluster.

To estimate malaria case incidence, a cohort of 25 children per cluster aged 6 months to 9 years will be randomly selected from a census list of children living in the study clusters and followed over 24 months. For malaria infection prevalence assessment, two cross-sectional surveys will be conducted at 6 and 18 months post-net distribution; 70 individuals per cluster will be randomly selected for each cross-sectional survey, stratified by age (< 5 years, 5–9 years, 10–14 years, ≥15 years and older) from each of the 60 clusters.

Routine cross-sectional entomological surveys using human landing catches (HLCs) will be conducted in all clusters to assess the human biting rate and EIR. Each cluster will be visited once every three months. Four households will be selected from a census list in each study cluster at each time point. The first house will be randomly selected by the study data manager, while the other three will be chosen by the field team, in a radius of 15–20 m around the first one, to facilitate the supervision of mosquito collectors.

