### Eligibility criteria

The cohort will include children aged 6 months to 9 years old resident in the study villages, without any severe illnesses and whose parents/carers have given written informed consent for their child to be included in the study. Inclusion criteria during cross-sectional surveys will be the willingness to participate and provide consent (or for parents/carers to provide consent for children); resident in the village during the previous 3 months, selected individuals without severe illness.

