#### Primary outcome

To assess whether the new dual-AI LLINs are superior to the reference LLIN, malaria case incidence in each intervention arm (Royal Guard and Interceptor G2) will be compared to malaria case incidence in the reference arm (Interceptor). To adjust for the increased risk of type I error due to multiple pairwise comparisons, the level of significance will be adjusted using the Bonferroni method. Following any treatment for malaria, a child will not be considered at risk for two weeks. Multilevel mixed models with random effects will be used to test the difference in incidence rate between each intervention and the control arm, allowing for repeated measurements on the same individual, and within-cluster correlation of responses. Survival analyses will be also used to compare time to the first infection case, adjusting for confounding factors using a Cox proportional hazards model. Multiple events will be allowed per child (with appropriate censoring to account for prophylactic protection following treatment and absence during follow-up visits).

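### The adjustment set stated for the primary incidence analysis does not name the child's age; prespecifying it would be a small, free gain in precision for both net comparisons

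*Protocol article*

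**What the plan says.** The protocol article's Statistical methods section gives one covariate rule for the primary analyses: they are by intention to treat and "adjusted for the restriction variables used for the constrained randomisation". The section on allocation and blinding names those variables: "population size of the cluster (required to balance net numbers), infection prevalence, and socio-economic status". It adds that "Data on these variables by cluster will be obtained through the pre-trial (baseline) cross-sectional survey".

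The Primary outcome paragraph under Statistical methods specifies a multilevel mixed model with random effects, "allowing for repeated measurements on the same individual, and within-cluster correlation of responses". It names no further covariate for that model. The additional time-to-first-event analysis is described as "adjusting for confounding factors using a Cox proportional hazards model", without listing the factors.

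On the cohort, Trial design says that "a cohort of 25 children per cluster aged 6 months to 9 years will be randomly selected from a census list", and Eligibility criteria that "The cohort will include children aged 6 months to 9 years old resident in the study villages". The objectives, outcomes and sample size sections give the upper age as 10 years. The census questionnaire is used "to collect demographic details on household residents" and to select the cohort. Trial status changes the cohort to 30 children per cluster followed for 21 months.

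**The concern.** Malaria incidence may differ by age across a range as wide as infancy to 9 or 10 years. The cohort is a simple random draw of 25 (now 30) children per cluster, with no age strata stated. The cross-sectional sample described in the same section is stratified by age. Age mix will therefore differ by chance between clusters and between arms. If age predicts incidence, that chance variation adds to the sampling variance of each cluster's rate, and so to the variance of both incidence rate ratios.

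A baseline covariate already held for every child could remove that component. Design power has no slack at the two-sided alpha of 1.67%, so even a small gain would be useful.

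**Working it through.** **Inputs from the Sample size section.** Rates 1.0 and 0.7 per child-year, between-cluster coefficient of variation k = 0.3, 20 evaluable children per cluster for 2 years (y = 40 child-years), 20 clusters per arm, two-sided alpha 1.67%, power 80%.

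**Step 1: reproduce the plan's figure.** The Hayes and Bennett formula for rates, without its added cluster, is

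c = (z_α/2 + z_β)² × [(λ0 + λ1)/y + k²(λ0² + λ1²)] / (λ0 − λ1)².

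- (2.393 + 0.842)² = 10.46
- Sampling term: 1.7/40 = 0.0425
- Between-cluster term: 0.09 × 1.49 = 0.1341
- Sum V = 0.1766
- c = 10.46 × 0.1766/0.09 = 20.5

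Power at 20 clusters is Φ(0.3/√(0.1766/20) − 2.393) = Φ(3.193 − 2.393) = 78.8%. With the extra cluster that the formula usually adds, c = 21.5 and power is 76.4%. The stated 20 clusters therefore reproduce approximately without the extra cluster. The calculation has no age term.

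**Step 2: share of variance that age cannot readily reach.** 0.1341/0.1766 = 76% is between-cluster variation. Age removes part of this only where age mix differs between clusters.

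**Step 3: add age.** Let CV_age be the between-child coefficient of variation of incidence due to age (an assumption; the protocol gives none). With m children sampled per cluster, the variance gains CV_age² × (λ0² + λ1²)/m. With m = 20, and age variation taken as additional to the design variance:

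| CV_age | Added variance | SE inflation | Power without age | Power with age |
|---|---|---|---|---|
| 0.2 | 0.0030 | 0.8% | 78.0% | 78.8% |
| 0.3 | 0.0067 | 1.9% | 77.0% | 78.8% |
| 0.5 | 0.0186 | 5.1% | 74.0% | 78.8% |
| 0.7 | 0.0365 | 9.9% | 69.6% | 78.8% |

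If age variation is instead taken to be already inside k = 0.3, adjustment raises power from 78.8% to 79.6%, 80.6%, 83.7% and 88.3% for the same four values.

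**Step 4: what those CVs mean, on the revised design.** Assume ages uniform from 0.5 to 10 years and a log-linear gradient with a youngest-to-oldest incidence ratio R. Then CV_age² = (ln R/2)(R + 1)/(R − 1) − 1, which gives CV_age = 0.20, 0.31, 0.455 and 0.58 for R = 2, 3, 5 and 8. Take 30 children less the same one-fifth loss (24 evaluable) for 1.75 years, so y = 42 and V = 1.7/42 + 0.1341 = 0.1746. The added variance, 1.49 × CV_age²/24, is 1.4%, 3.5%, 7.4% and 12.0% of V. Power without age is 78.7%, 77.7%, 76.0% and 73.9%, against 79.3% with it.

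**Step 5: simulation check.** Simulated cluster log rates (20 clusters per arm, 20 children, 2 years), unadjusted against age-standardised, gave an SD of the log rate ratio of 0.114 vs 0.113 at CV_age 0.23, 0.118 vs 0.112 at 0.47, and 0.125 vs 0.114 at 0.73. Power was 73.4% vs 74.6%, 69.2% vs 72.8%, and 64.5% vs 74.5%. The pattern agrees with the formula. The comparison is of cluster-level summaries, so it indicates the size of the effect and does not test the planned mixed model.

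**The case against.** **Covariate lists often belong in the analysis plan.** The text names the restriction variables without excluding others, and an analysis plan that is not shown could add age. A reader might infer that the primary model adjusts for these variables and nothing else; the protocol does not say so. What stands is narrower. The article does state an adjustment set for the primary analyses, and age is not in it. It mentions other factors where it intends them: unnamed confounders in the Cox analysis, and imbalanced factors in the entomological models.

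**The random effects already deal with age.** A reader might infer bias, invalid standard errors or a raised type I error. None follows. Selection within clusters is random, clusters are randomised, and the child and cluster random effects absorb unmodelled age variation. Chance imbalance is also small. With ages uniform over 9.5 years the SD is 9.5/√12 = 2.74 years. With 24 × 20 = 480 children per arm the standard error of the difference in mean age is 2.74 × √(2/480) = 0.18 years. At R = 3 that shifts the log rate ratio by (ln 3/9.5) × 0.18 = 0.02, against a standard error of about 0.11, and the interval already reflects it. This objection stands in full, so the loss is one of precision only.

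**The level of the restriction variables in the model is not stated.** They were obtained by cluster for the allocation, but household assets are also recorded for cohort children at enrolment, so a household-level socio-economic term is possible. That is correct, and the point about age does not depend on it.

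**The size rests on assumptions.** This also stands. The age distribution, the shape of the gradient and its steepness are all assumed, and with a shallow gradient the gain is under one point of power.

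**Conclusion.** This is a free improvement to the stated analysis, not an error in it. Leaving age out costs precision equally in the two comparisons, since both use the same model and the same control arm. For CV_age of 0.2 to 0.5 the standard error is inflated by about 1% to 5%, worth roughly 1 to 5 points of power. Losses near 10% in the standard error need CV_age around 0.7, which is steeper than an eightfold gradient under the uniform-age assumption. The gain cannot be large unless age heterogeneity is very strong, because between-cluster variation dominates and each cluster averages over 20 or more children. It is still worth taking, because design power by the plan's own inputs is 78.8%, or 76.4% with the extra cluster. The figures assume that age variation adds to the design variance and that adjustment removes the age component fully.

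**What to change.** In Statistical methods and its Primary outcome paragraph, prespecify the child's age at enrolment as a fixed covariate in the primary mixed model, alongside the restriction variables and for both comparisons. Fix one functional form in advance, for example linear plus quadratic, so that no choice remains after the data are seen. Keep the model with the restriction variables alone as a sensitivity analysis. If an analysis plan already includes age, the protocol text need only be aligned with it.

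The cost is one sentence and two model degrees of freedom for the linear plus quadratic form. Age is already needed to select the cohort, so no new data, visits or participants are required. With a log link the rate ratio keeps its interpretation.

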#### Primary outcome

To assess whether the new dual-AI LLINs are superior to the reference LLIN, malaria case incidence in each intervention arm (Royal Guard and Interceptor G2) will be compared to malaria case incidence in the reference arm (Interceptor). To adjust for the increased risk of type I error due to multiple pairwise comparisons, the level of significance will be adjusted using the Bonferroni method. Following any treatment for malaria, a child will not be considered at risk for two weeks. Multilevel mixed models with random effects will be used to test the difference in incidence rate between each intervention and the control arm, allowing for repeated measurements on the same individual, and within-cluster correlation of responses. Survival analyses will be also used to compare time to the first infection case, adjusting for confounding factors using a Cox proportional hazards model. Multiple events will be allowed per child (with appropriate censoring to account for prophylactic protection following treatment and absence during follow-up visits).

#### Secondary outcomes

Prevalence of malaria infection in the study clusters will be estimated at baseline, 6 months, and 18 months. The surveys will be analysed separately and in a combined model, controlling for the time in the analyses. All analyses will account for the multilevel nature of the data using random-effects regression models. The prevalence of moderate and severe anaemia in children under 5 will be analysed using logistic regression.

EIR will be estimated as the mean number of sporozoite infected *Anopheles* (*An. gambiae* s.I.) collected in the HLCs per house per night and weighted to account for the proportion of collected *Anopheles* processed for sporozoites. Differences in *Anopheles* density and EIR between the different arms will be estimated using random-effects negative binomial regression taking into account the intra-cluster correlation and any confounding factors that are found to be imbalanced between arms. Random effects logistic regression will be used to compare sporozoite rates between study arms allowing for within cluster correlation of responses.

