### Sample size

Sample size calculation for the primary outcome (malaria case incidence in children aged between 6 months and 10 years) was based on the method of Hayes and Bennett [39]. Based on passive data collected in 2018 by the NMCP in the study area, the mean number of malaria episodes per child per year in the reference arm was assumed to be 1. We assumed a between-cluster coefficient variation of 0.3 and that dual-AI LLINs will reduce malaria case incidence by 30% (i.e. to 0.7 cases per child per year). With a follow-up of 2 years, to detect this effect size with 80% power would require following 20 children and 5 additional children to account for the loss of follow-up (25 in total) in 20 clusters in each of the three arms. This sample size calculation includes adjustment for multiple testing (allowing for the 3 arms) using a Bonferroni-corrected two-sided alpha of 1.67%. This results in a total of 60 clusters required for the trial and a cohort of 1500 children.

For the cross-sectional surveys, it was assumed that malaria prevalence in the reference arm is 40%, with a coefficient of variation between clusters of 0.3. With 70 individuals per cluster and 20 clusters per arm, the study will have 80% power to detect a relative 30% lower prevalence (prevalence ratio 0.70) between each intervention arm to standard LLIN using a Bonferroni-corrected two-sided alpha of 1.67% to account for multiple comparisons.

To achieve adequate participant enrolment to reach the target sample size, enhanced community sensitization activities will be conducted before and during each activity in the community with the support of hamlet leaders and community health workers.

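### The 6- and 18-month prevalence models are not stated to adjust for cluster baseline prevalence, a restriction factor and the outcome's own baseline value; leaving it out makes intervals conservative and forgoes power

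*Protocol article*

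**What the plan says.** Under Assignment of interventions, the protocol article lists the restriction factors: "Arms will be balanced on the following criteria: population size of the cluster (required to balance net numbers), infection prevalence, and socio-economic status". It gives their source: "Data on these variables by cluster will be obtained through the pre-trial (baseline) cross-sectional survey". So each cluster has its own measured baseline infection prevalence.

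The opening paragraph of Statistical methods, above the subsections for primary and secondary outcomes, sets the adjustment rule: "All primary analyses will be conducted by intention to treat and adjusted for the restriction variables used for the constrained randomisation".

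The Secondary outcomes subsection then describes the prevalence analysis in three sentences. The first lists the survey rounds, with baseline among them: "Prevalence of malaria infection in the study clusters will be estimated at baseline, 6 months, and 18 months". The next sets out which models will be fitted: "The surveys will be analysed separately and in a combined model, controlling for the time in the analyses". The last deals with clustering: "All analyses will account for the multilevel nature of the data using random-effects regression models". No restriction variable is named there. For mosquito density and the entomological inoculation rate (EIR), the same subsection has a covariate rule of its own: "taking into account the intra-cluster correlation and any confounding factors that are found to be imbalanced between arms".

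**The concern.** Restricting the allocation on a prognostic cluster variable removes most of that variable's contribution to the difference between arms. If the model then omits the variable, its variance stays in the residual and the standard error describes a less precise trial than the one run. Intervals are too wide and the test rejects less often than its nominal level.

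Infection prevalence at 6 and 18 months is the secondary outcome for which this should matter most, because the restriction factor is the same quantity measured earlier. The rule is written for primary analyses, the prevalence text repeats none of it, and density and EIR follow a different rule. That makes it doubtful that the general rule reaches the secondary outcomes. At stake is a real effect on prevalence being reported as not significant, in a trial meant to inform a WHO review.

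**Working it through.** **Inputs from the Sample size section.** For the surveys "it was assumed that malaria prevalence in the reference arm is 40%, with a coefficient of variation between clusters of 0.3", so p0 = 0.40 and k = 0.3. The prevalence ratio of 0.70 gives p1 = 0.28. There are m = 70 people per cluster and c = 20 clusters per arm. Two-sided alpha is 1.67% (z = 2.394) and planned power 80% (z = 0.842).

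**Assumptions not in the article.** r is the correlation of true cluster prevalence between baseline and follow-up. The baseline survey is taken as 70 people per cluster; the article gives that number only for the 6- and 18-month surveys.

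**Step 1: the plan's own figure.** Hayes–Bennett variance per cluster pair:

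V = [p0(1−p0) + p1(1−p1)]/m + k²(p0² + p1²) = (0.24 + 0.2016)/70 + 0.09 × (0.16 + 0.0784) = 0.00631 + 0.02146 = 0.02776.

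The between-cluster share is 0.02146/0.02776 = 77%. SE = √(0.02776/20) = 0.03726. Power = Φ(0.12/0.03726 − 2.394) = Φ(0.827) = 79.6%. The required number of clusters is (2.394 + 0.842)² × 0.02776/0.12² = 20.2 per arm. The stated 80% is reproduced with no credit for adjustment. (Adding the formula's usual extra cluster would give 21.2 per arm, and 77.2% power at 20.)

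**Step 2: how well the baseline survey measures a cluster.** Reliability R = k²p0² / [k²p0² + p0(1−p0)/m] = 0.0144/(0.0144 + 0.00343) = 0.81.

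**Step 3: power with adjustment.** Replace k² by k²(1 − r²R). At r = 0.5 the between-cluster part is 0.02146 × (1 − 0.25 × 0.81) = 0.01712, so V = 0.02343, SE = 0.03423 and power = Φ(3.506 − 2.394) = 86.7%.

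| Assumed r | Interval width, adjusted/unadjusted | Power, adjusted | Gain over 79.6% (points) |
|---|---|---|---|
| 0 | 1.00 | 79.6% | 0 |
| 0.3 | 0.97 | 82.2% | 2.6 |
| 0.5 | 0.92 | 86.7% | 7.1 |
| 0.7 | 0.83 | 93.0% | 13.4 |
| 0.9 | 0.70 | 98.6% | 19.0 |

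**Step 4: simulation under restricted allocation.** 4,000 trials of 60 clusters per setting. Allocation was redrawn until the three arm means of observed baseline prevalence lay within 2 percentage points (an assumption; the article does not give the tolerance). One intervention arm was compared with control on cluster summaries, with and without observed baseline prevalence as covariate, at nominal alpha 1.67%.

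| Assumed r | Type I error, unadjusted / adjusted | Power, unadjusted / adjusted |
|---|---|---|
| 0 | 1.5% / 1.5% | 76.8% / 76.3% |
| 0.5 | 0.9% / 1.7% | 77.2% / 82.7% |
| 0.7 | 0.35% / 1.4% | 79.8% / 91.7% |
| 0.9 | 0.05% / 1.7% | 82.3% / 97.9% |

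The mechanism shows at r = 0.7 under no effect. The two estimates vary almost equally from trial to trial (standard deviations 0.0347 and 0.0342), yet the mean interval width is 0.2095 unadjusted against 0.1711 adjusted. The restriction has already made the estimate precise; the unadjusted model does not report it.

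**The case against.** The strongest reply is that the omission is inferred from silence. The adjustment sentence stands above both outcome subsections, and primary analyses can mean the main analysis of each outcome. On the narrow reading, intention to treat would not be stated for secondary outcomes either. The mixed-model sentence for the primary outcome names no restriction variable, yet nobody would conclude that it has none. The baseline round is listed among the surveys, so the combined model may already use it. A full analysis plan may settle all this.

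Much of that stands. A reader might infer that the prevalence comparisons ignore baseline prevalence; the article does not say so. What remains is that the wording permits two different models, that the separate density and EIR rule points to the narrow reading, and that including a baseline round in the combined model cannot help the separate 6- and 18-month models.

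Two further readings go too far. One is that the trial is underpowered without adjustment: the planned 80% was computed without it, so only an available gain is forgone. The other is a larger gain, to 83.7%, 90.7% and 98.3%, obtained by treating 0.3, 0.5 and 0.7 as correlations of observed prevalences. With reliabilities of about 0.81 and 0.77, an observed 0.7 implies a true correlation of about 0.7/√(0.81 × 0.77) = 0.89, across a replacement of nets throughout the area. Nothing in the article supports so high a value.

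**Conclusion.** The point holds as a matter of unclear scope with a known direction of harm. The 6- and 18-month prevalence models are not stated to adjust for cluster baseline prevalence, although the allocation was restricted on it. If it is left out, the separate comparisons are conservative: in simulation, type I error is 0.9% at r = 0.5 and 0.35% at r = 0.7 against a nominal 1.67%. Adjustment would narrow intervals by about 8% and 17% at those values. The power gain is about 7 and 13 points by formula, and 5.5 and 11.9 points in simulation. At r near zero nothing is lost.

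These sizes rest on the assumed r, a 70-person baseline survey and, for the simulation, the assumed balance tolerance. There is no threat of false positive findings. No benefit has been shown for anaemia, density or EIR, so the evidence does not support extending the rule to every secondary outcome.

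**What to change.** - In Secondary outcomes, state that the 6- and 18-month infection prevalence models include, as fixed covariates, each cluster's baseline infection prevalence (continuous, for example on the logit scale), cluster population size and socio-economic status.
- State how the baseline round enters the combined model: as a covariate or as an outcome, not both.
- In the opening paragraph of Statistical methods, make explicit whether the adjustment rule covers the main analysis of each outcome or only the primary outcome. The density and EIR covariate rule can stay as it is.

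The cost is about one sentence of text. The baseline data are already collected. Three covariates use about 3 of the 57 cluster-level degrees of freedom (60 clusters less 3 arms). If the correlation turns out near zero, the loss is negligible: 76.3% against 76.8% power in the simulation, which used one covariate.
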